**Figure 2 fig2:**
[figure not shown]
fNIRS data acquisition. **(A)** fNIRS scanning process diagram; **(B)** fNIRS channels location.

A portable fNIRS instrument (LIGHTNIRS, Shimadzu Corporation, Japan) will be utilized to measure cortical hemodynamic response, with a sampling rate of 13.33 Hz at wavelengths 780 nm and 830 nm. Due to PFC and S1 being ROIs of the mechanism hypothesis in this study, the optodes of fNIRS will be positioned over the prefrontal and bilateral primary somatosensory cortex. The fNIRS cap is created by 8 × 2 light sources and detectors (20 channels) placed according to the international 10–20 EEG system, with a separation distance of 2.5–3 cm for all optodes (Figure 2B). To achieve precise spatial registration, the Montreal Neurological Institute coordinates of all optodes will be measured using an electromagnetic 3D digitizer system, and the corresponding brain regions of the midpoint of each channel in the Brodmann Talairach template will be calculated.

### Data management

2.12

Clinical data will be managed through both paper and electronic case report forms (CRFs). Only outcome evaluators have access to CRFs and will perform double-data entry. The Evidence-based Medicine Center of the Affiliated Third Hospital of Chengdu University of Traditional Chinese Medicine will supervise the study and monitor the data regularly.

### Patient safety

2.13

In order to evaluate the risks caused by acupuncture, the safety assessment will be conducted after each acupuncture session. Adverse events such as hematoma, bleeding, severe pain, infection, fainting, or other severe events will be processed immediately, recorded with details in CRFs, and monitored by the Ethics Committees.

### Data analysis

2.14

#### Clinical data analysis

2.14.1

The primary clinical analysis will strictly follow the intention-to-treat (ITT) principle. Missing data will be handled using multiple imputation (MI) under the missing-at-random assumption, and sensitivity analyses will include per-protocol (PP) and complete-case analyses. The clinical data will be analyzed using SPSS 22.0 software. For the primary outcome (weekly mean 24 h-WI-NRS scores), a linear mixed-effects model (LMM) will serve as the primary analytic approach, including time, group, and their interaction as fixed effects, and a random intercept for each participant. In this primary model, the baseline measurement will be treated as the initial level of the time factor (Time = 0) rather than as a covariate, to avoid model misspecification and biased estimates. A pre-specified sensitivity analysis will additionally adjust for baseline outcome values and key demographics (age and sex) to test the robustness of the primary findings.

For secondary outcomes (measured at baseline and week 4), LMM will also be applied, with the same fixed and random effects structure as described above. If the LMM residuals violate normality assumptions, non-parametric alternatives (Wilcoxon signed-rank test for within-group comparisons; Kruskal-Wallis and Dunn test for between-group comparisons) will be applied. For the single-timepoint continuous data (instant cowhage-induced itch VAS, assessed only during the first fNIRS scanning), one-way ANOVA will be used if the data follow a normal distribution, or the Kruskal-Wallis test if not. To correlate fNIRS results with clinical outcomes, Spearman rank correlation will be used as a non-parametric alternative to Pearson correlation if normality assumptions are violated, and the false discovery rate (FDR) correction will be applied for multiple comparisons. The counting data will be analyzed using the chi-square test. The statistical significance threshold is set at 0.05 with the two-sided test.

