### Sample size

2.5

Since this trial will take the therapeutic effects of acupuncture on UP as the foundation and further explore its central mechanism via fNIRS, 24 h-WI-NRS will be used as the primary clinical outcome for this sample size calculation (Fishbane et al., 2020a, 2020b), with VA versus SA defined as the primary comparison; meanwhile, the WT group will serve as an auxiliary control to separate spontaneous disease fluctuation. Based on our preliminary pilot trial, the 24 h-WI-NRS mean differences were 3.68 ± 1.30 for the VA group and 1.64 ± 2.55 for the SA group after 4-week interventions compared to baseline. Using G*Power software with two-tailed tests, effect size = 1.01, *α* = 0.05, and 1-*β* = 0.95, this study requires 27 patients per group. Accounting for a 15% dropout rate, each group should enroll 32 patients; a total of 96 patients will be included across three groups.

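### The primary mixed model leaves baseline group means free, so it uses baseline inefficiently, and the baseline-adjusted sensitivity analysis, read literally, cannot test robustness

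*Protocol article*

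**What the plan says.** Section 2.14.1 (Clinical data analysis) makes a linear mixed model the primary analysis of the weekly mean 24 h-WI-NRS. Its fixed effects are time, group and time-by-group, with a random intercept per participant. On baseline it says that "the baseline measurement will be treated as the initial level of the time factor (Time = 0) rather than as a covariate", and it gives protection against misspecification and bias as the reason. Nothing constrains the groups to share a mean at Time 0.

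The next sentence reads: "A pre-specified sensitivity analysis will additionally adjust for baseline outcome values and key demographics (age and sex". Its stated purpose is to test robustness. The text does not say whether the Time 0 row then leaves the response. Missing values are to be multiply imputed.

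Section 2.5 (Sample size) works on change from baseline, "with VA versus SA defined as the primary comparison". Neither section 2.10.2 nor section 2.14.1 says which week, or which model contrast, is the treatment effect. The secondary outcomes, measured at baseline and week 4, take the same model structure.

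**The concern.** Two adjacent sentences fix the primary model and its robustness check, and they fit together badly.

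First, the reason for rejecting baseline as a covariate is not sound. Adjusting post-randomisation weeks for a value measured before randomisation does not bias a randomised comparison. With equal allocation and a large sample, it is also never less precise than the raw change score. The plan may therefore give up precision on data it already collects.

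Second, the sensitivity analysis may be empty. Baseline, age and sex do not vary within a patient. Added as main effects to a model that still has baseline among the responses, they cannot move a within-patient contrast. The two analyses would then agree however large a chance baseline imbalance was, and the agreement would be reported as robustness.

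**Working it through.** **The plan's own figure.** Inputs from section 2.5: "the 24 h-WI-NRS mean differences were 3.68 ± 1.30 for the VA group and 1.64 ± 2.55 for the SA group"; two-sided alpha 0.05; power 0.95.
- Pooled SD = √[(1.30² + 2.55²)/2] = √4.096 = 2.024.
- Effect size = (3.68 − 1.64)/2.024 = 2.04/2.024 = 1.008, against the stated "effect size = 1.01".
- The noncentral-t two-sample calculation gives 27 per group (power 0.954), which matches "this study requires 27 patients per group".
- 27/0.85 = 31.8, rounded up to 32, which matches "Accounting for a 15% dropout rate, each group should enroll 32 patients".

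The trial is thus sized on change scores, which is what the planned time-by-group contrast compares.

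**What the primary model estimates.** With complete data and group means free at Time 0, the week-4 time-by-group coefficient is (VA week 4 − VA baseline) − (SA week 4 − SA baseline), the difference in mean raw changes.

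**Precision.** Let r be the baseline-to-week-4 correlation and k the baseline SD divided by the week-4 SD. Both are assumptions and are taken as common to the arms. With week-4 variance set to 1:
- change-score variance is 1 + k² − 2rk;
- baseline-adjusted variance is 1 − r²;
- ratio = (1 − r²)/(1 + k² − 2rk), which reduces to (1 + r)/2 when k = 1.

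| r | ratio, k = 1 | ratio, k = 0.6 |
|---|---|---|
| 0.3 | 0.91/1.40 = 0.65 | 0.91/1.00 = 0.91 |
| 0.5 | 0.75/1.00 = 0.75 | 0.75/0.76 = 0.99 |
| 0.7 | 0.51/0.60 = 0.85 | 0.51/0.52 = 0.98 |

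The reduction in variance is 35%, 25% and 15% at k = 1, and about 9%, 1% and 2% at k = 0.6. The ratio is exactly 1 when r = k, so at k = 0.6 the gain vanishes at r = 0.6. The value 0.6 is an illustration: entry requires a weekly mean of at least 4, so baseline spans 4–10 while follow-up can span 0–10, and 6/10 = 0.6. Multiplied by the planned 27 per group and rounded up, the ratios correspond to 18, 21 and 23 at k = 1, and 25, 27 and 27 at k = 0.6.

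**Simulation.** There were 300 trials for each of r = 0.3, 0.5 and 0.7, with 32 per arm, five time points and equal variances (so k = 1 only). Mean SE of the week-4 VA-SA effect:

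| r | planned contrast | weeks 1–4, baseline as covariate | Time 0 kept, baseline means equal |
|---|---|---|---|
| 0.3 | 0.592 | 0.481 | 0.475 |
| 0.5 | 0.498 | 0.436 | 0.431 |
| 0.7 | 0.387 | 0.360 | 0.356 |

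The planned SE is about 23%, 14% and 8% larger than with baseline as covariate (0.592/0.481, 0.498/0.436, 0.387/0.360). The last column shows that keeping baseline as a response costs nothing once its means are constrained.

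**The sensitivity model read literally.** Baseline, age and sex were added and the Time 0 row was kept.
- Complete data, 900 trials: the largest difference from the primary time-by-group result was 7e-13 in the estimate and 8e-09 in the SE.
- Imputation makes each analysed data set balanced, so the identity carries over if both models use the same imputed sets.
- With 15% dropout and no imputation, the estimates differed by up to 0.17 points.
- The plain week-4 VA-SA difference (group effect plus interaction) did move, on average by 0.17, 0.25 and 0.30 points for r = 0.3, 0.5 and 0.7 with complete data.

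**The case against.** The best defence has four parts.

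- **Baseline as a response is a legitimate choice.** This stands. A reader might infer that placing baseline in the time factor is itself the fault, or throws the baseline away. Neither follows: the constrained model keeps baseline in the response without loss, and the change-score contrast does use baseline. In the simulation at r = 0.7 it was more precise than the unadjusted week-4 difference (SE 0.387 against 0.496). The inefficiency comes from the free baseline means.
- **The sensitivity analysis may switch model form.** The Time 0 treatment is stated for the primary model and set against baseline as a covariate, so the next sentence could mean a model of weeks 1–4 adjusted for baseline, which would be informative. This is a possible reading. A reader might infer that the check certainly cannot fail, but the article does not say that the Time 0 row is kept or that the time-by-group contrast is the treatment effect. Still, the adjustment is worded as an addition to the primary model and nothing removes the row. On the switched reading, the bias rationale for rejecting that same model as primary falls away.
- **The size of the gain is unknown.** This stands. A gain of 15–35% needs equal variances at baseline and week 4, which the entry cut-off makes doubtful.
- **Nothing is biased or underpowered.** This stands as well. The planned contrast is valid under randomisation and matches the quantity the trial was sized on.

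**Conclusion.** The point holds as one of efficiency and specification. The primary contrast is a raw change-score comparison that leaves the randomised equality of baseline means unused. Adjustment would lower its variance by 15–35% if baseline and week-4 SDs are equal and r lies between 0.7 and 0.3. If the SD ratio is 0.6, the gain at r = 0.3, 0.5 and 0.7 is only about 1–9%, and it is nil where r equals k. Since the article gives neither r nor k, no single figure can be claimed.

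The bias rationale is wrong if aimed at a post-baseline model. It is sound only as a warning against having baseline on both sides of one model, which is what the sensitivity sentence produces when taken literally.

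That analysis is uninformative by construction under three conditions: the Time 0 row stays in the response, the effect is the time-by-group contrast, and the data are balanced. Imputation supplies the third; sizing on change from baseline points to the second; the wording suggests the first without stating it. A reader should not conclude that the result would be biased or that 27, then 32, per group is too few. The secondary outcomes inherit the structure: with two time points, their interaction is also a change-score comparison.

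**What to change.** 1. Primary model: either keep Time 0 in the response and constrain baseline means to be equal across arms, or model weeks 1–4 with baseline and baseline-by-week as covariates.
2. Name the primary VA-SA contrast and the week at which it is evaluated.
3. State that any model with baseline as a covariate drops the Time 0 row from the response.
4. Keep the unconstrained change-from-baseline model as a sensitivity analysis, and enter age and sex with time interactions so that they can affect the contrast.
5. Delete the statement that using baseline as a covariate would give biased estimates.
6. Carry the same choices over to the secondary outcomes.

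The cost is wording in the protocol and analysis plan, settled before the analysis. No new data, visits or patients are needed, and the sample size calculation can stand.

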#### Instant itch intensity induced by the cowhage test

2.10.1

Patients will use VAS to rate itch intensity induced by the cowhage test during the first fNIRS scanning, with an evaluation per minute. The VAS scale ranges from 0 ~ 10, and the end-points anchoring the VAS are: 0 = no itch sensation, and 10 = maximum unbearable itch. The peak VAS itch score recorded during the observation period will be extracted for statistical analysis.

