#### Primary clinical outcome

2.10.2

The weekly mean 24 h-WI-NRS scores at baseline and during each week of the 4-week trial period will be evaluated as the primary clinical outcome (Fishbane et al., 2020a, 2020b). The 24 h-WI-NRS scale ranges from 0 (no itch sensation) to 10 (maximum unbearable itch) points.

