### Core neuroimaging indicator: fNIRS data acquisition

2.11

Based on the efficacy of acupuncture for UP, this study will further focus on its central mechanism. According to previous studies (Mochizuki and Kakigi, 2015; Sun, 2025), we hypothesize that acupuncture’s antipruritic effect of UP correlates with modulation of cortical regions involved in itch processing, particularly the prefrontal cortex (PFC) and primary somatosensory cortex (S1), which can be captured in real-time by portable fNIRS. Moreover, considering that the oxyhemoglobin (HbO) signal has a better signal-to-noise ratio and is more reliable and sensitive than the deoxyhemoglobin signal (Strangman et al., 2002; Dravida et al., 2018), this trial will use cortical HbO changes to characterize the functional activity of PFC and S1, two regions of interest (ROIs). Therefore, the HbO change of task-state scanning data during the first fNIRS scan will be the primary outcome of the immediate effect of acupuncture on relieving itch, and the resting-state scanning data after 0−/2−/4-week interventions will be the primary mechanistic outcome of acupuncture’s long-term effect on UP.

Patients will undergo three fNIRS recording sessions. Each fNIRS scan will be scheduled on non-dialysis days or before dialysis sessions to minimize the influence of acute biochemical fluctuations. The first fNIRS scan will be conducted before the long-term acupuncture treatment, including an 8 min rest scanning and a 5 min task scanning during acupuncture treatment with immediate itch induction by the cowhage test (Figure 2A). Another two fNIRS scans will be performed after the 6th and 12th long-term acupuncture treatments, with only the 8 min rest scanning.

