Given that the first fNIRS session includes both resting-state and task-state (cowhage-induced itch with VA or SA intervention, or WT control) scanning, while the 2−/4-Week-4 sessions only include resting-state scanning, these data will be analyzed separately according to different physiological states. Specifically, for the immediate effect of acupuncture antipruritus, the task-induced hemodynamic change (ΔHbO = task-state minus resting-state) during the first fNIRS scan will be calculated for each group. Since this is a single time-point measurement, the comparison (VA vs. SA vs. WT) of theseΔHbO values will be performed using one-way ANOVA. For the long-term effect of acupuncture antipruritus, only resting-state fNIRS data will be acquired at three time points (0−/2−/4-week). To account for the repeated-measures design across the three time points, LMM will be applied to longitudinal hemodynamic responses, with time, group, and their interaction as fixed effects, and a random intercept for each participant. The resting-state outcome measures will comprise: (1) regional HbO activity, defined as the temporal mean of the HbO concentration over the resting-state period for each channel; and (2) HbO-based functional connectivity, calculated as Fisher’s Z-transformed Pearson correlation coefficients between the time series of all channel pairs within and across the PFC and S1. The significance threshold is set to *p* < 0.05, and FDR correction will be strictly applied to control for multiple comparisons.

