### Limitations

3.4

However, several limitations should be acknowledged and managed. Firstly, uremic toxin level fluctuations in hemodialysis patients may affect cerebral hemodynamics. To address this, we will define strict dialysis adequacy criteria (spKt/V ≥ 1.2) in the inclusion criteria. Secondly, although the cowhage-induced itch model reliably activates non-histaminergic pruriceptive pathways relevant to UP, its intensity and temporal profile may differ from spontaneous uremic itch. Therefore, to address this limitation, we will perform additional analyses of resting-state brain activity and spontaneous itch perception during needle retention. In addition, with a detection depth of 20 mm approximately, fNIRS primarily measures cortical hemodynamics and cannot directly assess subcortical itch-related regions, such as the thalamus, insula, and brainstem. Future studies may utilize neuroimaging techniques with higher spatial resolution (e.g., fMRI) or multimodal approaches (e.g., fMRI-EEG) to further explore the central mechanisms of acupuncture for UP.

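### The peak cowhage itch score is compared without adjusting for baseline 24 h-WI-NRS, which is collected beforehand and may be prognostic; precision may be lost, but the test is valid

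*Protocol article*

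**What the plan says.** The cowhage rating is described as "instant cowhage-induced itch VAS, assessed only during the first fNIRS scanning", so the outcome has no pre-treatment value of its own. Section 2.10.1 reduces the per-minute ratings to one number: "The peak VAS itch score recorded during the observation period will be extracted for statistical analysis". Section 2.14.1 then fixes the test: "one-way ANOVA will be used if the data follow a normal distribution, or the Kruskal-Wallis test if not". No covariate appears there.

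The primary clinical outcome is "The weekly mean 24 h-WI-NRS scores at baseline and during each week of the 4-week trial period", so a baseline itch score exists for every patient. Adjustment for baseline outcome, age and sex is planned, but only as a sensitivity analysis of that primary outcome.

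Section 2.11 makes the task-state HbO change, not the VAS, the variable that "will be the primary outcome of the immediate effect of acupuncture on relieving itch". Section 2.5 sizes the trial on the 4-week change in 24 h-WI-NRS and states no power for the cowhage VAS.

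**The concern.** Patients enter with any weekly mean 24 h-WI-NRS of 4 or more. Sections 2.10.1 and 2.10.2 define two self-ratings of itch that both run from 0 to 10, from no itch to the worst unbearable itch. A patient with severe chronic itch, or one who habitually uses the top of such scales, may also rate cowhage itch higher. If so, baseline 24 h-WI-NRS explains part of the between-patient variance in the peak VAS, and a plain ANOVA leaves that part in the error term.

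What is at stake is the width of the interval for the VA–SA difference on the only scheduled patient-reported measure of the immediate effect. In addition, if the normality check sends the analysis to Kruskal-Wallis, the result is a rank test with no mean difference on the VAS scale.

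**Working it through.** **The plan's own figure.** Section 2.5 gives changes of 3.68 (SD 1.30) for VA and 1.64 (SD 2.55) for SA. Pooled SD = √((1.30² + 2.55²)/2) = 2.024, and d = (3.68 − 1.64)/2.024 = 1.008, against the stated 1.01. A two-sided two-sample t-test with α = 0.05 and power 0.95 needs 27 per group (power 0.954 at d = 1.01). Then 27/0.85 = 31.8, so 32 per group and 96 in total. The stated sample size reproduces, but it concerns the 4-week outcome.

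**Is the covariate available in time?** Table 1 places the 24 h-WI-NRS at week 0. The text puts the cowhage test at the first scan, before long-term treatment; Table 1 marks the VAS in treatment week 1. Under either placement, a baseline weekly mean can be complete before the test.

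**Effect of adjusting for it.** Inputs: three arms, n = 32 each, N = 96 (section 2.5); two-sided α = 0.05 (section 2.14.1). Assumed, because the documents are silent: a true VA–SA difference of d = 0.6 SD, and a correlation r between baseline 24 h-WI-NRS and peak VAS from 0 to 0.5. I use 32 and not 27 because the test takes place at the start, before most dropout.

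- Unadjusted: error df = 96 − 3 = 93, noncentrality = 0.6 × √(32/2) = 2.40, power 0.661.
- With k covariates: error df = 93 − k. The SE is multiplied by √[(1 − r²)(1 + k/(N − 4 − k))], and the noncentrality is 2.40 divided by that factor. The second bracket is the expected cost of chance covariate imbalance. It is 1 + 1/91 = 1.011 for k = 1 and 1 + 3/89 = 1.034 for k = 3.

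| r (R for three covariates) | SE ratio, k = 1 | Effective sample size, k = 1 | Power, k = 1 | Power, k = 3 |
|---|---|---|---|---|
| 0 | 1.005 | −1.1% | 0.656 | 0.646 |
| 0.1 | 1.000 | −0.1% | 0.661 | 0.651 |
| 0.2 | 0.985 | +3.0% | 0.674 | 0.664 |
| 0.3 | 0.959 | +8.7% | 0.697 | 0.687 |
| 0.4 | 0.922 | +17.8% | 0.731 | 0.722 |
| 0.5 | 0.871 | +31.9% | 0.779 | 0.769 |

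The SE breaks even where (1 − r²)(1 + k/(N − 4 − k)) = 1. That is r = √(1 − 1/1.011) ≈ 0.10 for baseline 24 h-WI-NRS alone, and R ≈ 0.18 if age and sex are added. At the same total correlation, adding age and sex costs about one point of power.

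These are powers for the VA–SA contrast with the three-arm pooled error, not for the three-group omnibus test that the plan names.

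**The case against.** The strongest reply is that nothing here is wrong. After 1:1:1 randomisation the unadjusted ANOVA gives a valid test and an unbiased difference, and covariate lists for a supporting outcome often sit in an analysis plan that is not shown. The first part stands in full. The second stands only in part, because the article does not leave the test open: it fixes an unadjusted one.

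The reply continues that the covariate is a different construct. A week of worst spontaneous itch is not the five-minute peak of induced itch during needling. Section 3.4 itself says that the intensity and time course of induced itch may differ from those of spontaneous itch. The entry threshold of 4 also truncates the covariate, which tends to lower a correlation. This stands too, and it is why the gain can only be given as a range.

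Three stronger readings are tempting, and the documents do not support them.

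- A reader might infer that precision is certainly being lost, or that chance imbalance in chronic itch biases the result. No correlation is documented, and the unadjusted standard error already allows for chance imbalance.
- A reader might extend the point to the task HbO change, because those "values will be performed using one-way ANOVA" as well. That variable is already task minus rest within the patient, and nothing in the documents suggests that weekly itch, age or sex predicts it.
- A reader might treat the VAS as the sole evidence for the immediate effect. The named primary outcome of that effect is HbO, and section 3.4 also mentions "additional analyses of resting-state brain activity and spontaneous itch perception during needle retention", though without an instrument or schedule.

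**Conclusion.** The point holds as a modest question of efficiency. The plan fixes an unadjusted comparison of the peak cowhage VAS while a plausible prognostic baseline value is already in hand. Under the assumptions above (d = 0.6, 32 per arm, one covariate), adjusting costs about half a point of power if the correlation is zero. It breaks even near r = 0.10, and gains about 4 points at r = 0.3, 7 at 0.4 and 12 at 0.5. Which of these applies cannot be known from the documents. The planned test is neither invalid nor biased. The case for change is that the possible gain is much larger than the possible loss.

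**What to change.** In section 2.14.1, replace the one-way ANOVA or Kruskal-Wallis test for the peak cowhage VAS by an ANCOVA with arm and the baseline weekly mean 24 h-WI-NRS, using the value completed before the cowhage test. Report the adjusted VA–SA difference with a 95% confidence interval. If residuals are skewed, which is quite possible for a peak on a bounded scale, use robust standard errors or a permutation p-value in place of a switch to a rank test, so that the estimate stays on the VAS scale. Age and sex are optional. Leave the analysis of task HbO change as it is on this point.

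The cost is one sentence in the plan and one error degree of freedom (three if age and sex are added). If the team prefers to keep the unadjusted test as the main analysis, the ANCOVA should at least be pre-specified as the supporting one.
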